#### Quality of Life

Disease-specific QoL will be assessed with the Functional Assessment of Cancer Therapy (FACT) – General which consists of the physical well-being (PWB), functional well-being (FWB), emotional well-being (EWB), and social well-being (SWB) subscales [52]. The FACT-Fatigue scale includes the 27 items from the FACT – General plus the 13-item fatigue subscale [52, 53]. On all scales, higher scores indicate better QoL and fewer symptoms. FACT-General and FACT-Fatigue both have good test-retest reliability with correlation coefficients of 0.92 and 0.87, respectively [52, 54].

General health-related QoL will be measured using the Short Form-12 (SF-12). The SF-12 is a 12-item, shortened version of the SF-36 assessing physical functioning, bodily pain, role functioning, emotional well-being, social functioning, energy/fatigue, and health perceptions [55, 56]. It also includes a single item that provides an indication of perceived change in health. The SF-12 has good test-retest reliability correlations of 0.89 and 0.76 for the physical and mental component score, respectively [55]. Additionally, scores from the SF-12 are highly correlated with scores from the complete SF-36 questionnaire [56]. The SF-12 has been previously used in cancer populations [57, 58].

#### Health and Disability

Disability will be assessed using the self-administered 12-item World Health Organization Disability Assessment Schedule 2.0 (WHODAS 2.0) [59]. This questionnaire is used to assess functioning in six major life domains (e.g., cognition, mobility, self-care, getting along, life activities, and participation) [59]. A simple scoring method will be used to sum the 12 items to create a Global Disability total score to describe any functional limitations. The scores for each item ranges from 1 (none) to 5 (extreme) [60]. WHODAS 2.0 has good test-retest reliability with and intra-class correlation coefficient of 0.98 [61].

#### Mental Health

Anxiety and depression will be assessed with the 14-item Hospital Anxiety and Depression Scale (HADS) [62]. The HADS provides anxiety and depression subscale scores and a total score. Each item is rated on a 4-point Likert scale (0 = “not at all”, 3 = “yes, definitely”), and higher scores are indicative of higher distress. The HADS scale has good reliability with intra-class coefficients of 0.92 and 0.88 for the anxiety and depression subscales, respectively [63].

#### Physical Function

Lower body strength will be assessed through the 30-second chair stand from the Senior Fitness Test [64]. This test will be adapted for remote delivery and self-administered by the participant and supervised by study personnel over Zoom [65]. The 30-second chair stand measures the number of full chair stands (seated to a full stand) that can be completed in 30 seconds. Participants will be asked to align a sturdy, non-rolling chair perpendicular to their computer so study personnel can see the full range of movement. Study personnel will start a stopwatch for 30 seconds and count the appropriate number of repetitions that the participant completes. A higher score indicates better lower body strength.

#### Patient Satisfaction

A patient satisfaction survey will be administered post-intervention to assess the satisfaction with the intervention by using researcher-generated, closed-ended questions: “Did the movement specialist effectively demonstrate constructive feedback throughout the program?” “The program workbook was informative and easy to follow?” The survey will assess the burden of the program and the participant’s feedback regarding the SB workbook, counseling sessions, and overall study experience. Likert scales ranging from 1 (not at all) to 7 (very much) will be used. This researcher-generated questionnaire is similar to measures employed in our prior work in PCS [30].

#### Demographic, Clinical, and Technology Literacy Information

The demographic variables include age, gender, marital status, highest level of education, current employment status, ethnicity, PA history, and height and weight to calculate body mass index (BMI). The medical variables include time since diagnosis, disease stage, current/prior treatments, previous recurrence, and current disease status, which have been used previously in studies with cancer survivors [20, 21, 66]. Technology literacy will be assessed using a modified version of the eHEALS ehealth literacy scale and 10 additional questions about internet and social media usage [67]. The eHEALS is an 8-item measure of eHealth literacy designed to measure combined knowledge, comfort, and perceived skills at finding, evaluating, and applying electronic health information to health problems [67]. The eHEALS has moderate stability with a test-retest correlations between 0.49 to 0.68 [67]. The eHEALS will be adapted to assess participants’ confidence in using and finding online information related to SB and PA specifically. The questions will assess general patterns of internet and social media use, including methods used to access the internet and social media, frequency of use, devices owned, and types of social media accounts owned [68].

##### Statistical Analyses

Linear mixed models will be used to model the primary outcome (i.e., SB) and secondary outcomes (i.e., LPA, motivational outcomes from M-PAC, QoL) at the three time points. Fixed effects included in the models will be time (i.e., baseline, 3-month, 6-month post-intervention), group (i.e., intervention, control), and the interaction. A random intercept will be included to account for variance between and within participants. All models will be estimated while adjusting for covariates (e.g., baseline SB, age, treatment type). Sensitivity analyses will be performed to test for informative dropouts.

The same analytic approach will assess subgroup differences of participants which will include several standard demographic (e.g., age, gender), fitness (e.g., baseline PA) and clinical variables (e.g., time since treatment, disease stage) by modeling the changes over time from post-intervention (F_1_: 3-months after baselines) to 6-month follow-up (F_2_: 9-months after baseline). An intention to treat analysis will be conducted based on all available data from PCS randomized regardless of non-adherence during the intervention. Participants with missing data will be included under the missing-at-random assumption of the mixed-model analysis.

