The primary objective is to determine the effects of the 12-week intervention (i.e., Fitbit + behavioral counselling) compared to a control condition (Fitbit + public resources) in reducing SB in PCS. It is hypothesized that the intervention group will decrease their SB compared to the Fitbit-only control condition at post-intervention (12 weeks) and 6-month follow-up. Secondary objectives are to determine the effects of the intervention on secondary outcomes including changes in MVPA, LPA, motivational outcomes from the M-PAC framework, physical function and patient-reported outcomes (i.e., QoL, fatigue, disability and mental health) compared to the Fitbit-only control group.

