### Study Design

The intervention is a two-armed, parallel groups randomized controlled trial. Following baseline assessments (T_1_), participants will be randomized to one of two groups: 1) an intervention group in which they receive a FitBit, SB workbook, and behavioral counselling or 2) a control group in which they receive a Fitbit and publicly available health education resources (Fitbit-only control). Follow up assessments will take place immediately after the 12-week intervention period (i.e., post-intervention; F_1_) and 9 months from baseline assessments (i.e., 6-month post-intervention; F_2_). The participant flow through the study is summarized in Fig. 1.

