#### Sample Size

A sample size calculation was performed in G*power based on a multivariate analysis of variance with two intervention levels (i.e., intervention, control) and two dependent variables (i.e., SB and PA). Based on our pilot trial with PCS, we assumed a medium effect size of Cohen’s *d* = 0.50 at the end of the intervention. Based on an alpha of 0.05 and power of 0.80, a total sample size of 100 is required. To account for the expected 20% attrition, a sample of 120 PCS (intervention *n* = 60, control *n* = 60) will be recruited.

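### A random intercept as the only stated covariance term forces one correlation across visits at 0, 3 and 9 months, and can bias the standard errors of both hypothesised contrasts in a direction the protocol cannot settle

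*Protocol article*

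**What the plan says.** The Statistical Analyses section of the protocol article plans linear mixed models for sedentary behavior (SB) and the secondary outcomes. On the mean structure it says: "Fixed effects included in the models will be time (i.e., baseline, 3-month, 6-month post-intervention), group (i.e., intervention, control), and the interaction". On the covariance it says only: "A random intercept will be included to account for variance between and within participants". It mentions no random slope, residual covariance structure or robust standard error. It adds: "All models will be estimated while adjusting for covariates (e.g., baseline SB, age, treatment type"), so baseline SB appears both as a level of the outcome and among the covariates. On missing data it says: "Participants with missing data will be included under the missing-at-random assumption of the mixed-model analysis".

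The Study Design section places the last assessment at "9 months from baseline assessments (i.e., 6-month post-intervention; F_2"), so the visits fall at 0, 3 and 9 months. The objectives at the end of the Background predict that the intervention group will "decrease their SB compared to the Fitbit-only control condition at post-intervention (12 weeks) and 6-month follow-up". Both follow-up comparisons therefore belong to the primary hypothesis.

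**The concern.** A random intercept with independent residuals is compound symmetry: one variance at all visits, and one correlation for gaps of 3, 6 and 9 months alike. Under that model the between-arm contrasts in change at 12 weeks and at 9 months get the same variance when data are complete. If the two true variances differ, at least one reported SE is wrong. Even if they are equal, the common value can miss both.

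The error rate and power of both primary comparisons are at stake. An SE that is too large makes a test conservative and costs power; one that is too small lets the type I error rise above 5%. The analysis also relies on the likelihood under missing at random, with 20% attrition expected (Sample Size). A misspecified covariance can then affect the estimates as well as their SEs. That second effect is not quantified here.

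**Working it through.** **Inputs from the article.** Three visits at 0, 3 and 9 months (Study Design); a random intercept only (Statistical Analyses); 60 participants per arm and 20% attrition (Sample Size). The article has no figure on this point to reproduce. It gives no SD of SB and no between-visit correlation, and its sample-size statement (it "assumed a medium effect size of Cohen’s *d* = 0.50 at the end of the intervention", with 100 evaluable and 120 recruited) implies neither. All correlations and SDs below are therefore assumptions.

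**Formula.** With complete data and independent residuals, the random-intercept model estimates every change variance as 2 × (mean variance − mean covariance). With equal variances scaled to 1:

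- model change variance = 2(1 − mean ρ), the mean being over the three visit pairs
- true change variance at visit t = 2(1 − ρ₀ₜ)
- SE ratio k (model/true) = √[(1 − mean ρ)/(1 − ρ₀ₜ)]
- actual type I error of a nominal two-sided 5% test = 2[1 − Φ(1.96k)]

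**Decay example.** Mean ρ = (0.7 + 0.6 + 0.5)/3 = 0.6, so the model variance is 2 × 0.4 = 0.80. The true variances are 2 × 0.3 = 0.60 at 12 weeks and 2 × 0.5 = 1.00 at 9 months. The ratios are √(0.80/0.60) = 1.155 and √(0.80/1.00) = 0.894. At 12 weeks, a contrast with a true power of 80% would fall to Φ(2.80 − 1.96 × 1.155), about 70%.

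**Follow-ups closer to each other.** Mean ρ = (0.5 + 0.7 + 0.5)/3 = 0.567, so the model variance is 0.867. The true variance is 1.00 at both visits, and both ratios are √0.867 = 0.931.

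| Assumed ρ: 0–3 / 3–9 / 0–9 months | SE ratio 12 wk | SE ratio 9 mo | Type I 12 wk | Type I 9 mo |
|---|---|---|---|---|
| 0.6 / 0.6 / 0.6 | 1.00 | 1.00 | 5.0% | 5.0% |
| 0.65 / 0.6 / 0.55 | 1.069 | 0.943 | 3.6% | 6.5% |
| 0.7 / 0.6 / 0.5 | 1.155 | 0.894 | 2.4% | 8.0% |
| 0.9 / 0.81 / 0.729 (0.9 per 3 months) | 1.367 | 0.831 | 0.7% | 10.4% |
| 0.5 / 0.7 / 0.5 | 0.931 | 0.931 | 6.8% | 6.8% |
| 0.6 / 0.75 / 0.5 | 0.979 | 0.876 | 5.5% | 8.6% |
| 0.5 / 0.55 / 0.6 | 0.949 | 1.061 | 6.3% | 3.8% |
| 0.65 / 0.6 / 0.55 with SDs 1, 1.3, 1.1 | 1.03 | 1.03 | 4.3% | 4.3% |

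In the last row the mean variance is (1 + 1.69 + 1.21)/3 = 1.30 and the mean covariance is (0.845 + 0.858 + 0.605)/3 = 0.769. The model variance is 2 × (1.30 − 0.769) = 1.06, against true values of 1.00 at both visits.

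**Check with dropout, and with baseline entered in different ways.** REML simulation under the null: 60 per arm, 10% missing at 12 weeks and 20% at 9 months, 1,500 runs per setting. SE ratios at 12 weeks / 9 months:

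| Use of baseline SB | ρ 0.7 / 0.6 / 0.5 | ρ 0.5 / 0.7 / 0.5 |
|---|---|---|
| Outcome level | 1.16 / 0.85 | 0.94 / 0.93 |
| Outcome level, arms constrained equal | 1.12 / 0.95 | 0.97 / 1.00 |
| Covariate only | 1.09 / 0.88 | 0.99 / 1.03 |
| Both outcome level and covariate | 1.12 / 0.83 | 0.91 / 0.92 |

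Under the decay pattern with baseline as an outcome level, type I error was 2.3% and 9.3%. The closed form is thus a fair guide to the mechanism, but the size moves with how baseline enters.

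**The case against.** **The article does not say that the random intercept stands alone.** It says one will be included. A residual structure or robust SEs could be set in the full protocol or analysis plan, which are not shown, and their absence from an article is no fault in itself. This is fair as far as it goes. But the sentence gives the random intercept the task of covering variance both between and within participants, which leaves no role for another term. Read as written, it states a model. If the full plan uses a different one, the sentence misdescribes it.

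**A directional reading goes too far.** A reader might infer that the 12-week SE will be too large and the 9-month SE too small, so that the primary test loses power and the maintenance claim is tested above its nominal level. The article does not support this. It needs correlation that decays with the gap and roughly equal variances, and the article reports neither. This design makes another pattern credible: participants are screened on high self-reported SB, both arms receive a Fitbit after baseline, and both follow-ups come after the intervention. Baseline may then correlate less with either follow-up than the follow-ups do with each other, and both SEs come out too small. The table also shows a reversed case and a case with both too large. This objection stands in full against any fixed direction or single magnitude.

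**A random intercept is a common choice for three visits.** It is, and with equal correlations and variances it costs nothing for the change contrast. For a raw between-arm difference at one visit with complete data, the correlations drop out and equal SDs suffice. So the choice is a needless restriction rather than an outright error.

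**Conclusion.** The concern holds in conditional form. As written, the covariance model imposes one variance and one correlation across unequally spaced visits, while the primary hypothesis uses two different follow-up contrasts. If the true covariance differs, the model-based SEs are generally wrong. Over the assumed patterns in the first table, the change-contrast SE ratios run from 0.95 or less to well above 1 at 12 weeks (0.931 to 1.367) and from 0.831 to 1.061 at 9 months; type I error runs from 0.7% to 6.8% and from 3.8% to 10.4% respectively. These are illustrations under assumed correlations and SDs, for unadjusted contrasts with complete data. They do not predict this trial's results, and the direction cannot be read from the article.

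That uncertainty is itself the reason to drop the restriction: the unstructured model needs no guess about the pattern. This is a cheap improvement worth making before analysis, not a defect that invalidates the design.

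**What to change.** In Statistical Analyses, replace the random-intercept sentence with wording such as: *Visit will be treated as categorical, with an unstructured within-participant covariance matrix, estimated by REML with Kenward-Roger degrees of freedom. If this model does not converge, a heterogeneous Toeplitz structure, or a random intercept with robust (sandwich) standard errors, will be used.* Fix the order of the two fallbacks in advance and apply the rule to the primary and secondary models.

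State also whether baseline SB enters as an outcome level or as a covariate, not both. With an unstructured covariance, a model that uses it both ways can fit baseline exactly, so the baseline variance collapses and the fit fails.

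Cost: one or two sentences and a different covariance option. With three visits there are six covariance parameters instead of two, hence four extra, for 120 participants. The downside is those parameters and a possible need for the fallback. No new data are required.

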#### Blinding

Study personnel and participants will be blind to group allocation during baseline as randomization will take place after completion of all baseline measures. Subsequent data collection appointments will be completed by study personnel that are blind to the group allocation. Due to the nature of the study, it is not possible to blind the participants to their group allocation.

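### The only window named for subgroup differences is F1 to F2, after the intervention has ended, so it measures who keeps the effect rather than whether the intervention effect differs between subgroups

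*Protocol article*

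**What the plan says.** The Statistical Analyses section sets out a linear mixed model for the three assessments: "Fixed effects included in the models will be time (i.e., baseline, 3-month, 6-month post-intervention), group (i.e., intervention, control), and the interaction". For subgroups it continues: "The same analytic approach will assess subgroup differences of participants". It lists examples of demographic, fitness and clinical variables (age, gender, baseline PA, time since treatment, disease stage), and then gives the method: "by modeling the changes over time from post-intervention (F_1_: 3-months after baselines) to 6-month follow-up". No subgroup contrast that starts at baseline is stated anywhere in the article.

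Three other places fix the context:
- Study Design, on timing: "Follow up assessments will take place immediately after the 12-week intervention period (i.e., post-intervention; F_1_) and 9 months from baseline assessments".
- Blinding, on when allocation happens: "randomization will take place after completion of all baseline measures".
- Background, final paragraph, on the hypothesis: "the intervention group will decrease their SB compared to the Fitbit-only control condition at post-intervention (12 weeks) and 6-month follow-up".

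**The concern.** The active phase runs from baseline to F1, and "The primary objective is to determine the effects of the 12-week intervention". A subgroup analysis placed beside that objective will naturally be taken to ask whether the intervention works better in some men than in others. A contrast that begins at F1 starts after the effect has been produced. It asks whether the two arms drift apart or together over the following six months, and whether that drift differs by subgroup.

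The two questions can have different answers. A subgroup with a large and lasting benefit has nothing to show between F1 and F2. A subgroup that gained most also has most to lose. If the result were reported as who responds, advice on whom to offer the programme could point the wrong way.

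**Working it through.** The protocol gives no subgroup figure to reproduce, so the check is contrast algebra followed by illustrations.

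**Inputs from the article.** Randomisation follows baseline (Blinding). The intervention ends at F1 (Study Design). The subgroup contrast is F1 to F2 (Statistical Analyses). The planned sample is 120 with 20% attrition (Sample Size).

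**Assumed, because the article does not give them.** Subgroup effects, the fraction of effect retained, the SD and the within-person correlation.

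**Step 1: what each contrast estimates.** Let D1(s) and D2(s) be the benefit in subgroup s at F1 and F2, that is, the reduction in SB in the intervention arm relative to control, with positive values good. The expected arm difference at baseline is zero. Then:
- baseline to F1 estimates D1(s)
- baseline to F2 estimates D2(s)
- F1 to F2 estimates D2(s) - D1(s)

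**Step 2: interactions between subgroups A and B.** Write I1 = D1(A) - D1(B) and I2 = D2(A) - D2(B). The F1-to-F2 interaction is I2 - I1. It is zero when the subgroup difference persists unchanged. When A gains more, it is negative whenever that advantage shrinks.

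**Step 3: proportional retention.** If each subgroup keeps a fraction k of its F1 effect, the F1-to-F2 interaction is (k - 1) x I1. With D1(A) = 0.7 SD and D1(B) = 0.3 SD, I1 = 0.4 SD.
- k = 1: (0.7 - 0.7) - (0.3 - 0.3) = 0
- k = 0.5: (0.35 - 0.7) - (0.15 - 0.3) = -0.20 SD, while I2 = 0.35 - 0.15 = +0.20 SD

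**Step 4: a range of losses, in min/day.** Take D1(A) = 60 and D1(B) = 20, so I1 = 40.

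| Loss after F1 | Interaction at F1 | Interaction at F2 | F1-to-F2 interaction |
|---|---|---|---|
| 0% | 40 | 40 | 0 |
| 25% | 40 | 30 | -10 |
| 50% | 40 | 20 | -20 |
| 75% | 40 | 10 | -30 |
| 100% | 40 | 0 | -40 |

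**Step 5: unequal retention.** Let A fall from 60 to 30 and B from 20 to 15. The F1-to-F2 changes are -30 and -5, an interaction of -25. Yet A does better at both visits: I1 = 60 - 20 = 40 and I2 = 30 - 15 = 15.

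**Step 6: cases without reversal.** If both subgroups lose the same absolute amount, say 10, the result is (50 - 60) - (10 - 20) = 0. If effects grow by a quarter after F1 (k = 1.25), it is 0.25 x 40 = +10, the same sign as I1.

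**Step 7: simulation of the 50% case.** This used 120 x 0.8 = 96 completers in four equal cells, SD 100 min/day, correlation 0.6 and 2000 runs. Mean interactions were 39.6 (baseline to F1), 19.2 (baseline to F2) and -20.4 (F1 to F2). The estimate favoured A in 85%, 70% and 28% of runs respectively.

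**The case against.** Four points on the other side carry weight.

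- **Maintenance is a declared interest.** The Discussion makes maintenance of behaviour change a focus of the trial, and the hypothesis extends to 6-month follow-up. Who keeps the change once support stops is a proper subgroup question, and the F1-to-F2 interaction answers it correctly. This stands, and it is why the contrast should be kept. But the text does not label it as maintenance; it offers it as the assessment of subgroup differences in general.
- **Baseline may stay in the model.** Subgroups are to be handled by the same approach as the main analysis, which includes baseline. Baseline-anchored contrasts could then be taken from the same fit. A reader might infer that the trial cannot show who benefits; the article does not support that, because it never says the subgroup model is confined to F1 and F2. The sentence may even be a loose reference to both follow-up visits. If so, it still needs rewording, because the contrast it names is F1 to F2.
- **The contrast is not biased.** A reader might infer bias because F1 is measured after randomisation. The change is still compared between randomised arms, and the named adjustment is for baseline SB, not F1. The F1-to-F2 interaction is a different estimand from the interaction at F1, not a wrong-signed estimate of it. The criticism is one of relevance.
- **The sizes are assumed.** No subgroup effect or rate of loss comes from the article, and Step 6 shows patterns without reversal. The figures show what can happen, not what is expected.

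**Conclusion.** The point holds in a limited form. The one subgroup window that the article names addresses differential maintenance or loss. It does not address whether the effects hypothesised at 12 weeks and at 6-month follow-up differ between subgroups. This is a contrast the article states, not detail left to a statistical analysis plan.

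If the result is read as showing who benefits, a fully maintained 0.4 SD interaction appears as 0, and one where both effects halve appears as -0.2 SD. That a fully maintained interaction vanishes is algebra and needs no assumption about SD or correlation. Reversal requires the larger benefit to shrink more in absolute terms, as it does under proportional fading. It would go too far to say that subgroup conclusions will be wrong: that depends on how effects evolve after F1 and on how the result is reported, and the article does not say it will be reported as response to the 12-week programme.

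The consequence is confined to the subgroup analysis. The objectives contain no subgroup hypothesis, the sample size does not rest on one, and the primary comparison is untouched.

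**What to change.** Reword the subgroup sentence in Statistical Analyses. In the planned mixed model with all three time points, add group x subgroup x time terms and name two contrasts as the subgroup analysis: baseline to F1 and baseline to F2. Keep the F1-to-F2 contrast as a separate analysis, labelled as addressing maintenance, and state that it does not show which subgroup gained more from the intervention.

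The data are already scheduled at all three visits (Data Collection, Table 2), so nothing further needs to be collected. The only cost is a few more exploratory contrasts to report.
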